The ambitious goal to eliminate new pediatric HIV infections by 2030 requires accelerated prevention strategies in high-risk settings. Several approaches could be pursued. In contrast with adult individuals at high risk of HIV acquisition, the universal and equitable access to pre-exposure prophylaxis (PreP) is so far not available to children [4], despite clinical trial evidence.

Innovative biomedical solutions, including long-acting, injectable formulations, offer a paradigm shift in the pediatric HIV epidemic [5]. Modified HIV-1 bNAbs are highly potent and long-acting, and therefore have the indisputable potential for preventing MTCT perinatally and postnatally. Indeed, bNAbs for infant prophylaxis were identified as a potentially safe and durable option by the WHO-led “Paediatric Antiretroviral Drug Optimization group” and as a priority for drug development [6].

On the basis of modelling data available we propose to test the antibody directed to the CD4-binding site (CD4-bs e.g. VRC07-523) and combine it with an antibody to the V2-glycan supersite (CAP256V2). Many of the bNAbs have been engineered to enhance their therapeutic potential. Modification of the Fc-region of the bNAbs by an “LS” mutation increases binding to neonatal Fc-receptors, improving protection against lentiviral infection in non-human primates [7] and extending the bNAbs half-life to 4–6 months in adults [8]. Furthermore, isolation of more potent bNAbs (e.g. CAP256V2LS) [9] and engineering of bNAbs to increase potency (e.g. VRC07-523LS) [10] has made subcutaneous (SC) administration a realistic option in neonates and infants. Such extended half-life and elevated potency would enable protection of breastfeeding infants during the first year of life with as few as 2–3 administrations. In addition, they become particularly interesting as the volume of each administration would not exceed 1.5 ml, given the high bNAb concentration in formulations (100–150 mg/ml).

The aim of our study is to define the optimal dose(s), the ideal combination(s) of bNAbs (potency and breadth) and timing of SC administration to prevent infant HIV acquisition from birth and through breastfeeding in high-incidence countries such as South Africa.

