**Description of Arms**					
	**N**	**Study product**	**Dose (mg/Kg)**	**Time (from birth)**	**Recruitment**
**Arm 1:**	8	CAP256V2LS	5	< 96 h	Sequential
**Arm 2:**	8	CAP256V2LS	10	< 96 h	Randomized
**Arm 3:**	8	CAP256V2LS	20	< 96 h	Randomized
**Arm 4:**	8	VRC07-523LS	20	< 96 h	Randomized
**Arm 5**	8	VRC07-523LS	30	< 96 h	Randomized
	**N**	**Study product**	**Dose (mg)**	**Time (from birth)**	**Recruitment**
**Arm 6**	8	CAP256V2LS + VRC07-523LS	60 + 90	< 96 h	Sequential
**Arm 6b**		CAP256V2LS + VRC07-523LS	120 + 120	3 months (12 weeks)	Same infants of arm 6

Based on emerging safety data of arms 1 to 5 [11] and PK (to be published), which were adjudicated by the internal study safety committee (ISSC), independent (external) safety medical committee (ISMC) and the Data Safety and Monitoring Board (DSMB), arm 6/6b includes a fixed dose of each antibody at each time point. Furthermore, the discussions confirmed that it would be best if the second doses were administered at 12 weeks (Table 2).

**Table 2 Tab2:** summarizes the step wise proceeding of the trial according to safety data

**Step 1**		Product* for dose 1	Dose 1	Timing for dose 1	Product for dose 2		Dose 2	Timing for dose 2
Arm 1:		CAP256V2LS	5 mg/kg	0- < 96 h	No second dose			

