##### Secondary objectives

To evaluate the PK profile up to 6 months of each single bNAb administered, at different doses within 96 hours of birth in breastfeeding HIV exposed neonates born without HIV (arms 1 through 5).To evaluate the PK profile up to 3 months of bNAbs administered in combination, at different doses within 96 hours of birth in breastfeeding exposed neonates without HIV (arm 6).To evaluate the PK profile up to 6 months of each bNAb, administered in combination, in breastfeeding exposed neonates without HIV infants after a second administration at 3 months (arms 6/6b).To assess safety (AE) up to 6 months after each single bNAb (arms 1 to 5), up to 3 months after the first combined bNAbs administration (arm 6) and up to 6 months after the second administration of the combined bNAbs (arm 6b).

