#### Secondary analyses on secondary endpoints

AEs rates, expressed as number of events divided by number of person-days of follow-up and calculated by univariate Poisson regression, will be also estimated among enrolled neonates.

Pharmacokinetic parameters will be estimated by a non-compartmental analysis (NCA) performed using WinNonlin® version 8.0 (Certara, St. Louis, MO, USA) applied on data collected from neonates who completed the study. The primary PK endpoints will be: clearance, maximum plasma concentration (C_max_) and area under the concentration–time curve (AUC) from time zero to the last quantifiable time point (AUClast). C_max_ values will be compared with those at baseline (pre-administration of bNAbs) using the Wilcoxon signed-rank test. Bioequivalence between study arms will be assessed using the geometric mean ratio (GMR) and 90% confidence interval (90% CI) of AUClast and C_max_. The conventional bioequivalence criterion of 0.80 will be used.

The other endpoints of the trials will be summarized with descriptive analyses; they will be described according to the study arm and, if assessable, by month of follow-up until a maximum of 6 months since first or second bNAbs administration, using means with standard deviations or medians with interquartile ranges or ranges or 95%CI for quantitative variables, and proportions with their 95% CI for qualitative or categorical variables. Non-parametric tests that will be considered to test changes in continuous measures during follow-up are: Wilcoxon signed-rank test or Friedman test.

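### AUClast spans about 6 months in arms 1–5 but about 84 days after the first dose in arm 6, so it is not like-for-like if arm 6 or 6b enters the bioequivalence ratios

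*Protocol article*

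**What the plan says.** Under *Secondary analyses on secondary endpoints*, the protocol article makes clearance, Cmax and AUC the primary PK endpoints. AUC is taken "from time zero to the last quantifiable time point (AUClast". It then states: "Bioequivalence between study arms will be assessed using the geometric mean ratio (GMR) and 90% confidence interval (90% CI) of AUClast and C_max", and "The conventional bioequivalence criterion of 0.80 will be used". It does not name the arms to be compared, say which dose starts the clock in arm 6/6b, or fix a common interval.

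*Secondary objectives* gives three PK horizons:

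- **Arms 1–5:** "To evaluate the PK profile up to 6 months of each single bNAb administered".
- **Arm 6:** "To evaluate the PK profile up to 3 months of bNAbs administered in combination".
- **Arm 6/6b:** up to 6 months "after a second administration at 3 months (arms 6/6b".

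The text under Table 1 records the view that it would be best if "second doses were administered at 12 weeks". Tables 1 and 2 show that arm 6b consists of the arm 6 infants. First doses there are 60 mg CAP256V2LS and 90 mg VRC07-523LS; second doses are 120 mg of each.

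On persistence, *Background and rational* describes the LS mutation as "extending the bNAbs half-life to 4–6 months in adults", and *Study products* gives VRC07-523LS an adult half-life above 3–4 months. No infant half-life is stated.

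**The concern.** AUClast depends on how long concentrations are followed. For an antibody that declines slowly, much of the area lies after day 84. Arms 1–5 collect that later area and arm 6 cannot, because the second dose ends its first-dose profile. The second-dose profile then starts on top of residual first dose, which raises its AUC and Cmax and makes a per-dose clearance (dose divided by AUC) too low.

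This matters because arm 6 against arms 3 and 5 is the only same-product comparison in the trial that is nominally dose-matched. At 3 kg, 60/3 = 20 mg/kg (arm 3) and 90/3 = 30 mg/kg (arm 5). Among arms 1–5, same-product pairs differ in dose by design. A reader wanting to know whether giving the antibodies together changes exposure would look at arm 6 against arms 3 and 5, and the window alone could produce an apparent answer.

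**Working it through.** The article states no AUC, ratio or PK precision figure, so there is nothing to reproduce.

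**Inputs**

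- First-dose window in arm 6: 12 weeks = 84 days (text under Table 1; Table 5).
- Window in arms 1–5: 6 months, taken as 182 days, with 168 days as the alternative (*Secondary objectives*; Table 4).
- First/second dose, D1/D2: 60/120 = 0.50 for CAP256V2LS; 90/120 = 0.75 for VRC07-523LS (Tables 1 and 2).
- Half-life t: 90–180 days spans the article's adult values (3–4 and 4–6 months). Shorter values are assumptions, since no infant value is given.
- Model: one compartment, first-order decline, rapid absorption, no growth dilution, identical kinetics in all arms.

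**Window effect.** With equal dose the true ratio is 1.00. The AUClast ratio of arm 6 (first dose) to a single-dose arm is

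(1 − 2^(−84/t)) / (1 − 2^(−182/t)).

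At t = 120 days: (1 − 0.616)/(1 − 0.350) = 0.384/0.650 = 0.59.

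**Carry-over.** Residual first dose as a share of the second dose's own AUC is (D1/D2) × 2^(−84/t). At t = 120 days: 0.50 × 0.616 = 0.31 and 0.75 × 0.616 = 0.46.

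| Half-life (days) | AUC ratio, 84 vs 182 days | Carry-over, CAP256V2LS | Carry-over, VRC07-523LS |
|---|---|---|---|
| 20 | 0.95 | 3% | 4% |
| 30 | 0.87 | 7% | 11% |
| 40 | 0.80 | 12% | 17% |
| 60 | 0.71 | 19% | 28% |
| 90 | 0.63 | 26% | 39% |
| 120 | 0.59 | 31% | 46% |
| 180 | 0.55 | 36% | 54% |

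**Crossing point.** The ratio falls below 0.80 once t exceeds about 40 days. With 168 days it simplifies to 1/(1 + 2^(−84/t)), which equals 0.80 at t = 42 days; at 90, 120 and 180 days it is then 0.66, 0.62 and 0.58.

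**Sensitivity to absorption.** Assumed absorption half-lives of 1.5 and 4 days lower the window ratios by at most about 0.025. The 1.5-day value raises carry-over by at most about 0.01.

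**Clearance.** If second-dose AUC is inflated by 26–54%, dose/AUC is too low by 1 − 1/1.26 = 21% to 1 − 1/1.54 = 35%.

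**A different time zero.** If AUClast in arm 6/6b ran from the first dose to the end of follow-up (84 + 182 = 266 days, both doses), it would be about 3.0–3.3 times (CAP256V2LS) or 2.3–2.6 times (VRC07-523LS) the single-dose AUC over half-lives of 15–180 days. The direction of the distortion therefore depends on which reading is adopted.

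**After the fix.** With AUC over days 0–84 after the first dose in every arm, identical kinetics and dose give a ratio of 1.00.

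**The case against.** The strongest reply is that the disputed comparison is not written down. The bioequivalence sentence names no pairs. Arm 6 against arms 3 and 5 is listed only under *Descriptive and univariate analyses*, for baseline characteristics, and no PK objective asks whether co-administration alters exposure. Ratios within arms 1–5 share one planned window and are untouched. This stands, and it makes the point conditional. It does not remove it: the text fixes AUClast for comparisons between arms without excluding arm 6, and a SAP that used a partial AUC would depart from that text.

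A reader might go further and infer that all arm 6/6b exposure ratios are wrong by construction. The documents do not support that:

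- The first-dose Cmax ratio is affected by neither truncation nor carry-over.
- Arm 6b has a 6-month window of its own, so its problem is carry-over and a different dose, not truncation.
- Time zero is undefined for arm 6/6b, so even the sign of the bias is not settled.
- The size rests on adult half-lives. The text under Table 1 says that PK from arms 1–5 has already been reviewed, so the trial team can judge which row of the table applies.

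Two further replies also stand. Total concentration after the second dose, residual included, is the right quantity for the proportion of children above the target concentration; carry-over is a bias only for exposure or clearance credited to the second dose. And a common window does not make arm 6 against arms 3 and 5 a clean comparison: arm 6 is recruited sequentially, and 60 mg is 15–30 mg/kg over the eligible birth weights of 2.0–4.0 kg. A population PK model or a particular limit on extrapolated AUC would be a preference, not a correction.

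**Conclusion.** The point holds conditionally. If arm 6 or 6b enters the between-arm ratios, AUClast as fixed in the article does not measure the same thing in both arms. At the article's adult half-lives (90–180 days) the first-dose ratio would be about 0.55–0.63 with no true difference, and the 0.80 criterion would be missed for any half-life above about 40 days. Residual first dose would add about 26–36% (CAP256V2LS) or 39–54% (VRC07-523LS) to second-dose AUC. At a half-life of 20 days or less both effects are about 5% or smaller. These figures assume mono-exponential decline, equal dose and no growth dilution. The consequence is limited to secondary PK results; the primary safety endpoint is not affected.

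**What to change.** In the PK paragraph:

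1. Name the arm pairs for the ratio analysis and define time zero for each dose in arm 6/6b.
2. For arm 6 (first dose) against arms 3 and 5, replace AUClast by the partial AUC over days 0–84 after the first dose. The month 3 visit in arms 1–5 has a window of ±14 days and the day 84 visit in arm 6 one of +7 days, so state how concentrations are interpolated to day 84.
3. Take Cmax for that ratio from visit days common to both schedules. Table 5 has a day 1 visit that Table 4 lacks; both have days 3, 14 and 28.
4. Keep the 6-month AUC for arms 1–5.
5. Do not use uncorrected second-dose AUC or Cmax in between-arm ratios or to derive per-dose clearance. Either correct for the residual first-dose concentration or report them as total exposure.
6. Report arm 6 against arms 3 and 5 as descriptive, since it is non-randomised and mixes fixed-mg with mg/kg dosing.

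The cost is a few sentences and a small amount of analysis time, with no new visits or samples. The price is that concentrations after day 84 in arms 3 and 5 do not contribute to that one ratio.

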## Methods

### Study products

In this protocol the bNAbs CAP256V2LS, never tested in pediatric populations, and VRC07-523LS were chosen based on the following characteristics:epitope complementarity (CD4bs and V1V2-glycan) to target different viral regions involved in cell entry;breadth for subtype C (dominant in South Africa) and other subtypes to cover also viruses circulating in other high prevalent areas beside South Africa;half-life > 3–4 months in adults (VRC07-523LS), allowing large administrations intervals with the goal of providing the least number of administration during the breastfeeding period;potency and availability of the formulation for SC administration, which in children is preferable to intravenous administration;CAP256V2LS safety assessment in adults (CAPRISA 012B trial) showed no serious adverse events, and adverse events did not result in study product discontinuation;VRC07-523LS safety assessment in the IMPAACT P1112 phase I pediatric study showed that the product is generally well tolerated, none of the severe adverse events reported were related to the study product or resulted in study product discontinuation in any participant.availability through non-profit partnerships and a Target Product Profile plan to reduce costs of production.

The Vaccine Research Center (VRC), National Institute of Allergy and Infectious Diseases (NIAID), National Institutes of Health (NIH) developed VRC07-523LS, while CAP256V2LS has been developed by VRC, together with Centre for the AIDS Programme of Research in South Africa (CAPRISA). The VRC, NIAID, NIH is the sponsor of the original U.S. Food and Drug Administration (FDA) investigational new drug application (IND) to evaluate the potential clinical uses of CAP256V2LS and VRC07-523LS.

CAP256V2LS and VRC07-523LS are both recombinant human immunoglobulin G1 (IgG1) antibody produced in the Chinese Hamster Ovary (CHO) DG44 cell line in accordance with the current Good Manufacturing Practice (cGMP) regulations. The VRC Pilot Plant-VCMP is a qualified manufacturer for the release of Investigational Medicinal Products and labels clinical vials for the trial, and it manufactured, tested and released the master cell bank. Both products are approved for use in South Africa under clinical trial conditions. Neither product is subject to agreement with companies or other organizations for supply of the products.

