### Assignment of interventions

#### Sample size calculation

A total of 48 breastfeeding HIV exposed uninfected eligible neonates will be enrolled in the study (8 neonates recruited in each arm). Power calculations were not performed for this study, given that it is a Phase 1 trial aiming to test safety and PK in a small number of participants [12]. The trial objectives specifically state an evaluation of safety that did not include comparing safety between arms; thus there was no need to perform power calculation. We have, however, carefully evaluate and presented the probability of observing at least one event under various hypothetical SAE rates and this forms the key sample size consideration. The enrolment of 48 neonates will allow the study to have 8 infants per arm (target sample size of each arm is 6) in the final safety dataset in the hypothesis of a 25% of lost to follow-up.

The probabilities reported in Table 6 highlight the likelihood of the study to detect either rare or common SAEs (Table 6). According to the reported probabilities, there is 11% chance of getting 2 SAEs in a sample of 8 participants when the true SAE proportion is 50% (i.e. common) and 5% when the true SAE proportion is 5% (i.e. rare). In addition, there is 0.4% chance of getting 0 (no) SAEs in a sample of 8 participants when the true SAE proportion is 50% (i.e. common) and 66% when the true SAE proportion is 5% (i.e. rare).

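### The planned Wilcoxon test of C_max against the pre-dose level carries no information about exposure: its p-value is set almost entirely by the number of infants

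*Protocol article*

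**What the plan says.** The protocol article, Secondary analyses on secondary endpoints, describes a non-compartmental analysis "applied on data collected from neonates who completed the study". It goes on: "The primary PK endpoints will be: clearance, maximum plasma concentration (C_max_) and area under the concentration–time curve (AUC"; the AUC meant is AUClast. It then commits to a paired test: "C_max_ values will be compared with those at baseline (pre-administration of bNAbs) using the Wilcoxon signed-rank test". The sentence is not limited to any arm or dose. No purpose, significance level or sidedness is given, and it is not said whether the test is run by arm.

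The pre-dose concentration is not stated anywhere, but several sections bear on it:

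- Study products describes each product as a "recombinant human immunoglobulin G1 (IgG1) antibody produced in the Chinese Hamster Ovary (CHO) DG44 cell line".
- Table 1 and Interventions and study procedures place the first dose within 96 h of birth, and the only second dose (arm 6b) at 3 months in the infants of arm 6.
- The maternal exclusion criteria rule out concurrent HIV immunotherapy or another investigational product.
- The infant exclusion criteria rule out infants who have had, or are expected to need, blood products or immunoglobulin.

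On numbers, Sample size calculation says: "A total of 48 breastfeeding HIV exposed uninfected eligible neonates will be enrolled in the study (8 neonates recruited in each arm". It gives "8 infants per arm (target sample size of each arm is 6" as the basis, "in the hypothesis of a 25% of lost to follow-up".

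**The concern.** A signed-rank test asks whether paired differences are centred on zero. Here each difference is the highest concentration after an injection minus the concentration before it. Where no product was present beforehand, the difference is positive for any infant who absorbed a measurable amount. Even where some product was present, comparing a maximum of several values with one earlier value favours a positive difference.

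If all differences are positive, the test statistic takes its extreme value and the p-value depends only on how many infants are analysed. It would be the same for ample exposure and for exposure far below target. The trial's aim is to define optimal doses, and a small p-value attached to a primary PK endpoint could be read as evidence of adequate exposure when it is no such evidence.

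**Working it through.** **Inputs.** From Sample size calculation: 8 enrolled per arm, target 6, 25% loss, 48 in total. From Secondary analyses on secondary endpoints: signed-rank test, PK analysis in completers only. From Study products: "half-life > 3–4 months in adults (VRC07-523LS". Assumed, because not stated: testing by arm, two-sided, exact p-value, and 0.05 where a threshold is mentioned.

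**The plan's own figure.** 6 / (1 − 0.25) = 8 per arm, and 6 enrolled arms × 8 = 48 (arm 6b re-uses the infants of arm 6). Both reproduce. The plan gives no p-value, power or other figure for the C_max test.

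**First dose (arms 1 to 5 and arm 6).** Under the null hypothesis, each of the 2^n patterns of signs is equally likely. If all n differences are positive, the negative rank sum is 0, only one pattern is that extreme in that direction, and the two-sided p is 2/2^n.

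| Infants analysed | Exact two-sided p |
|---|---|
| 8 | 2/256 = 0.0078 |
| 7 | 2/128 = 0.0156 |
| 6 | 2/64 = 0.0313 |
| 5 | 2/32 = 0.0625 |
| 4 | 2/16 = 0.125 |

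The size of C_max does not enter. This was checked on simulated C_max sets against a zero baseline, with medians from 0.01 to 500 (a 50,000-fold range) and log-scale SDs from 0.05 to 1.0. Every set of 8 gave 0.0078125 and every set of 6 gave 0.03125. The normal approximation is also a constant for each n (0.0117 for 8, 0.0277 for 6).

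**Baseline not exactly zero.** With a background of 0 to 2 units against a C_max near 100, p for 8 infants stayed at 0.0078125. The result needs only that each C_max exceeds that infant's own baseline.

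**Pooling.** If infants were pooled by antibody in step 1, the formula is unchanged: 2/2^24 = 1.2 × 10^-7 for the 24 CAP256V2LS infants (arms 1 to 3) and 2/2^16 = 3.1 × 10^-5 for the 16 VRC07-523LS infants (arms 4 and 5). The p-value is smaller but no more informative.

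**Second dose (arm 6b).** Carry-over is likely. If the adult half-life held in infants with simple exponential decline, a half-life of 3 months would leave 0.5^(3/3) = 50% of the concentration after 3 months, and one of 4 months would leave 0.5^(3/4) = 59%. With the trough set at 10%, 30%, 60% and 90% of the second-dose C_max, p for 8 infants was still 0.0078125. It moves only if some infant's post-dose maximum lies below the pre-dose level:

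- One such infant, with the smallest difference: 2 patterns are as extreme, so p = 2 × 2/256 = 0.0156.
- Two such infants, with the two smallest differences: 5 patterns have a negative rank sum of 3 or less, so p = 2 × 5/256 = 0.0391.

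**The case against.** The strongest reply is that little hangs on this test. That is largely right, and it limits the point in these ways:

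- **Other inference on C_max exists.** A reader might infer that this is the only inferential procedure for a primary PK endpoint. It is not: the same section plans geometric mean ratios with 90% CIs between arms for AUClast and C_max against a bioequivalence criterion. It is the only within-arm comparison named for C_max.
- **No dose decision depends on it.** A reader might infer that the p-value would steer dose choice. No section says so. Step progression rests on 28-day safety reviews, and Study design says that the fixed doses of arm 6/6b followed committee review of safety and PK data from arms 1 to 5. Adequacy of exposure has its own secondary endpoint, the proportion of children above the target concentration.
- **It is not a false positive.** If every infant's C_max exceeds baseline, the null is false and rejecting it is correct. The fault is triviality, not type I error.
- **Significance in every arm is not assured.** No significance level or by-arm testing is stated. PK is restricted to completers, and arm 6b can lose infants under the second-dose criteria. With 5 or fewer, the exact test cannot reach an assumed 0.05, however high the exposure.
- **A nil baseline is inferred.** The maternal exclusion covers only concurrent immunotherapy, and the article gives no assay specificity or quantification limit.

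All five stand. None gives the test a use, because the argument needs only that each post-dose maximum exceeds its own baseline.

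**Conclusion.** The concern holds as a defect of one planned analysis. Run by arm, the comparison should return 0.0078 for 8 infants or 0.031 for 6 (exact, two-sided) at any dose and for either antibody. It therefore says nothing about exposure and should not be reported as a result for a primary PK endpoint. No other section of the article narrows or repairs it.

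For the first dose the conclusion rests on the inference that pre-dose levels are nil or near nil. For arm 6b it rests on the near certainty, not the guarantee, that the maximum after a new dose exceeds the trough. The figures assume by-arm, two-sided, exact testing.

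The impact is modest. It concerns a secondary analysis, and the other PK summaries do not depend on it. The documents do not support going further and saying that dose selection, safety decisions, the primary endpoint or the sample size are compromised.

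**What to change.** Delete the C_max-versus-baseline test and replace the sentence with estimation:

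- Report geometric mean C_max with a 95% CI by arm and antibody, beside the already planned proportion of infants above the target concentration. The section on descriptive analyses already foresees by-arm summaries with 95% CIs, so this fits the existing plan.
- Use the sample before the first dose only as an assay check.
- For arm 6b, report the concentration before the second dose as the trough, and describe the rise above it without a test.

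A slope of log C_max on log dose across arms 1 to 3 could be added as an exploratory description of dose proportionality. It is optional: arm 1 was not randomised, arms 2 and 3 belong to separate randomisation rounds, and each has only 6 to 8 infants.

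The cost is one sentence in the protocol or SAP. No new data or samples are needed, and all that is lost is an uninformative p-value.

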**Methods:**

Two bNAbs, CAP256V2LS and VRC07-523LS, will be assessed in a sequential and randomized phase I, single-site, single-blind, dose-finding trial. We aim to investigate the 28-day safety and pharmacokinetics (PK) profile of incrementally higher doses of these bNAbs in breastfeeding HIV-1 exposed born without HIV neonates alongside standard of care antiretroviral (ARV) medication to prevent (infants) or treat (mothers) HIV infection.

The trial design includes 3 steps and 7 arms (1, 2, 3, 4, 5, 6 and 6b) with 8 infants in each arm. The first step will evaluate the safety and PK profile of the bNAbs when given alone as a single subcutaneous (SC) administration at increasing mg/kg body weight doses within 96 h of birth: arms 1, 2 and 3 at doses of 5, 10, and 20 mg/kg of CAP256V2LS, respectively; arms 4 and 5 at doses of 20 and 30 mg/kg of VRC07-523LS, respectively. Step two will evaluate the safety and PK profile of a combination of the two bNAbs administered SC at fixed doses within 96 h of birth. Step three will evaluate the safety and PK profile of the two bNAbs administered SC in combination at fixed doses, after 3 months. Arms 1 and 6 will follow sequential recruitment, whereas randomization will occur sequentially between arms (a) 2 & 4 and (b) 3 & 5. Before each randomization, a safety pause will allow review of safety data of the preceding arms.

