#### Descriptive and univariate analyses

All the available safety data of each participant will be considered in the analyses; these data will be classified as severity (grade), expectedness, and potential relatedness (causality) to the study intervention. Descriptive analyses will be performed according to the study arm and the endpoints will be summarized using means with standard deviations or medians with interquartile ranges or ranges or 95% confidence intervals (CI) for quantitative variables, and proportions with their 95% CI for qualitative or categorical variables; CIs will be calculated using the exact method.

Given the small sample size of the study arms, there will be no statistical power for a formal test of differences between study arms with respect to safety. The analyses will check for clinically relevant differences in the main baseline maternal and infant characteristics between the following study arms: 2 vs 3, 4 vs 5, 6 vs 3 and 5; the presence of relevant imbalances in these characteristics among arms will be eventually tested by calculating differences [between means (standardised effect size) or proportions] with the corresponding 95% confidence intervals.

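### The planned bioequivalence verdicts between step 1 arms are fixed by the dose ratio or compare different antibodies, and the meaningful arm 6 contrasts are distorted by body weight, AUC window and small numbers

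*Protocol article*

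**What the plan says.** The Protocol article's section Secondary analyses on secondary endpoints plans: "Bioequivalence between study arms will be assessed using the geometric mean ratio (GMR) and 90% confidence interval (90% CI) of AUClast" and of Cmax. It adds: "The conventional bioequivalence criterion of 0.80 will be used". The section names no arm pairs, no dose normalisation and no upper bound. It also says that Cmax "values will be compared with those at baseline (pre-administration of bNAbs) using the Wilcoxon signed-rank test", and it restricts the non-compartmental analysis to neonates who completed the study.

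The arms are set out in the abstract's Methods and in Table 1:

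- CAP256V2LS alone: "arms 1, 2 and 3 at doses of 5, 10, and 20 mg/kg of CAP256V2LS, respectively".
- VRC07-523LS alone: "arms 4 and 5 at doses of 20 and 30 mg/kg of VRC07-523LS, respectively".
- Arm 6: both antibodies at fixed doses of 60 mg and 90 mg, with a second administration at 12 weeks (arm 6b).

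On allocation, "randomization will occur sequentially between arms (a) 2 & 4 and (b) 3 & 5". The only list of between-arm comparisons is in Descriptive and univariate analyses, where it serves the baseline checks: "2 vs 3, 4 vs 5, 6 vs 3 and 5".

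**The concern.** Bioequivalence asks whether two ways of giving the same nominal dose of the same substance produce the same exposure. The step 1 arms were built to differ, either in dose or in antibody. Applied to un-normalised AUClast and Cmax, the criterion mostly returns the dose ratio that the design put in.

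At stake is how the secondary PK results are read. The plan could report arms as not bioequivalent where that was settled in advance. Under the one-sided reading it could report a doubled exposure as bioequivalent. In the arm 6 contrasts, a shorter AUC window could look like an effect of combining the antibodies.

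**Working it through.** **Inputs from the document.** Doses as above. Eight infants per arm, with a target of 6 after 25% loss (Sample size calculation); check: 6 / (1 − 0.25) = 8, which reproduces the plan's figure. No power was calculated. Birth weight 2.0–4.0 kg (Infant inclusion criteria). PK follow-up is 6 months for single antibodies and 3 months for the first combined dose (Secondary objectives); Table 5 places the second dose at day 84.

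**Assumed, not in the document.** Between-infant CV 15–50%; dose-proportional exposure; half-lives as stated in step 3.

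**1. Step 1 pairs, same antibody.** The true un-normalised GMR equals the dose ratio: 10/5 = 2, 20/10 = 2, 20/5 = 4, 30/20 = 1.5. The test was simulated as two parallel log-normal arms with a pooled-variance 90% t-interval (200,000 runs, CV 15–50%):

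| True GMR | Passes 0.80–1.25 (6 or 8 per arm) | Passes 0.80 only, 8 per arm | Passes 0.80 only, 6 per arm |
|---|---|---|---|
| 1.5 (arm 5 / 4) | at most 0.11% | 81–100% | 69–100% |
| 0.667 (arm 4 / 5) | at most 0.11% | at most 0.9% | at most 1.1% |
| 2 (arm 2 / 1 or 3 / 2) | 0.00% | 98–100% | 93–100% |
| 0.5 (reversed) | 0.00% | at most 0.02% | at most 0.06% |

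The pair 3 / 1 (ratio 4) is more extreme in both directions. The randomised pairs, 2 with 4 and 3 with 5, set CAP256V2LS against VRC07-523LS. Bioequivalence of two different molecules has no meaning, so no arithmetic applies.

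**2. Arm 6 against 3 and 5: dose ratio.** 60 mg over 2.0, 3.0 and 4.0 kg is 30, 20 and 15 mg/kg; 90 mg is 45, 30 and 22.5 mg/kg. Relative to 20 mg/kg (arm 3) and 30 mg/kg (arm 5), the ratio is 1.5, 1.0 and 0.75 for both antibodies.

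**3. Arm 6 against 3 and 5: AUC window.** With identical PK and single-exponential decline, the AUClast ratio of an 84-day to a 180-day profile is (1 − e^(−84k)) / (1 − e^(−180k)), where k = ln 2 / half-life:

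- 30 days: 0.856 / 0.984 = 0.87
- 40 days: 0.767 / 0.956 = 0.80
- 60 days: 0.621 / 0.875 = 0.71
- 120 days, in the region of the adult half-lives the article cites: 0.384 / 0.646 = 0.59

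**4. Arm 6 against 3 and 5: precision.** The half-width on the log scale is t(0.95, 2n − 2) × √ln(1 + CV²) × √(2/n). For n = 8 and CV 30%: 1.761 × 0.2936 × 0.5 = 0.2585. An observed GMR of 1.0 then has a 90% CI of 0.77–1.30, outside 0.80–1.25. Setting the half-width equal to ln 1.25 gives the largest observed CV at which any pass is possible: about 26% with 8 per arm and 22% with 6. The chance of a 0.80–1.25 pass when the true GMR is 1:

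| CV | 8 per arm | 6 per arm |
|---|---|---|
| 15% | 77% | 56% |
| 20% | 39% | 20% |
| 30% | 4% | 1.8% |
| 40% | 0.3% | 0.2% |
| 50% | <0.1% | <0.1% |

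For 80% power, about 15, 31, 52 and 78 per arm would be needed at CVs of 20, 30, 40 and 50%.

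**5. Cmax against pre-dose.** Before the first dose an infant has received no bNAb, so every difference should be positive. The exact two-sided signed-rank p-value is then 2/2⁸ = 0.0078 with 8 infants and 2/2⁶ = 0.031 with 6, whatever the dose.

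**The case against.** The case on the other side has several parts, and much of it stands.

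- A reader might infer that these comparisons say nothing about PK at all. That is not so. Arm 6 against 3 and arm 6 against 5 compare the same antibody at nominally the same mg/kg at 3.0 kg, with and without the partner antibody. That is a genuine exposure question, and both pairs are in the list used for baseline checks.
- A reader might take 0.80 as a deliberate one-sided bound. The article calls the criterion conventional, which may be shorthand for 0.80–1.25. A doubled exposure passes only on the literal reading with the higher dose as numerator. The two readings give opposite results for such pairs, so the text should not permit both.
- A reader might infer that even identical arms cannot pass. A GMR of exactly 1 is required only at the limiting CV. With 8 per arm, an observed GMR of about 0.91–1.10 passes at CV 15%, and about 0.95–1.05 at CV 20%. The CV is not given, so how far sample size decides the result is conditional.
- A reader might infer that dose proportionality goes unexamined. Clearance is a planned endpoint and is already dose-adjusted, so comparing it across arms is informative. PK curves, half-life and the proportion above the IC80 target are also planned.
- Arm pairs, windows and normalisation are commonly left to an SAP, and the article does not say outright that arm 6's 3-month AUC will be set against a 6-month one. But the measure, the verdict and the criterion are stated here, and used as written they give the results above.
- The Cmax objection concerns the first dose only. Before the second dose in arm 6b, residual antibody may be present.

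**Conclusion.** The concern holds for a stated secondary PK analysis. For arms 1, 2 and 3, and for 4 against 5, the un-normalised verdict is set by the dose ratio if exposure is dose-proportional: at most about 0.1% chance of passing 0.80–1.25, or a result determined by the choice of numerator under 0.80 alone. For 2 against 4 and 3 against 5, the question has no meaning.

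The arm 6 contrasts are worth keeping, but not as written. The dose ratio runs from 1.5 to 0.75 with weight. The AUClast window alone gives 0.87, 0.80 or 0.71 at assumed half-lives of 30, 40 or 60 days, and less for longer ones; infant half-lives may differ from the adult values. A 0.80–1.25 pass is impossible above an observed CV of about 22–26% and unlikely at an assumed CV of 20% or more. The first-dose Cmax test carries no information.

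This should be fixed, but it does not threaten the trial's main conclusions. A reader might infer that a wrong dose could be chosen because of it. The document does not support that: the primary endpoint is safety, escalation follows safety review, the arm 6/6b doses were already set from emerging safety and PK data reviewed by the committees, and no dose decision is tied to the bioequivalence result.

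**What to change.** In Secondary analyses on secondary endpoints:

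1. Remove the bioequivalence verdict and the 0.80 criterion. Dose normalisation alone would not rescue the verdict at these numbers unless the CV is about 15% or less.
2. Within each antibody only, report GMRs with 90% CIs of AUC and Cmax, normalised to the mg/kg each infant actually received, and present them as estimates. The contrasts are arms 1–3 (for example a power model with slope and CI), 5 against 4, 6 against 3 for CAP256V2LS, and 6 against 5 for VRC07-523LS.
3. Use a common window, AUC from 0 to 84 days, for every contrast with arm 6's first dose.
4. Delete the first-dose Wilcoxon comparison of Cmax with baseline.

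The cost is wording only: the same samples, visits and software serve. The sponsor gives up a nominal equivalence claim that these arms could not support.
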